### Outcome assessment

2.7

A variety of measures are included at the T0, T1, and T2 evaluations. The primary outcome measure is improvement in memory recall. Recall will be assessed using the word-association task during the learning phase at visit one (T0), 7 (T1) and 28 (T2) days after learning during NITESGON.

#### Primary outcome measures

2.7.1

*Word-association task.* Subjects will perform a Swahili–English word association task, based on a well-known paradigm [20]. Subjects will be asked to learn a list of 50 Swahili–English word pairs (e.g. mashua–boat) selected from previously published norms [20]. Subjects will learn the list of word pairs across a total of 3 blocks, in which each block consists of a study (S) and test (T) phase. The study phase of each block will consist of 50-word pairs followed by a test phase of the 50 words. During study trials, subjects will see each Swahili word and its English translation on a computer screen simultaneously for 5 s and will be told to study the word pairs so that they can recall the English word when given the Swahili word. After every study period, there will be a 30-s rest period (consolidation). During the test trials, subjects will be presented with the Swahili word and asked to type the correct English translation. Each test trial will last 16 s, after which the computer program will automatically advance to the next item regardless of whether the patient has entered a response. If subjects fail to recall an item during testing, they will not be given any feedback. In the following Blocks 2 and 3, subjects will study the entire list in each study phase but only items that they had not yet recalled in the previous block will be tested in the test phase. Subjects will then be dismissed and asked to return for a follow-up test 7 days and 28 days later (recall phase). During this test, subjects will be shown each Swahili word for 16 s and asked to type the correct English translation. This is identical to the test phase from the learning period.

#### Secondary outcome measures

2.7.2

(1)Neurophysiology. Rest-state EEG will be collected immediately before and after NITESGON (T0) and will be correlated with the recall of the word-association task 7 (T1) and 28 (T2) days after NITESGON.(2)TES Adverse events*.* We will use the NITESGON exit questionnaire developed by Brunoni et al. [21] to assess potential side-effect (headache, neck pain, scalp pain, tingling, itching, burning sensation, skin redness, sleepiness, trouble concentrating, mood changes) at the end of T0.(3)Blinding. At the end of the experiment (T2), subjects will be asked if they thought they were assigned to the control or active group.(4)Control assessments. We will collect the California Verbal Learning Test II, Delis Kaplan Color Word Interference Test, Beck Depression (BDI) and Anxiety Inventory (BAI), Trial A & B, COWAT and DIGIT Span to verify that the effect obtained cannot be associated due to differences between groups on these control measures. These will be collected during visit 1 before NITESGON (T0), and 28 days after NITESGON (T2).

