In a recent study we demonstrated that non-invasive transcutaneous electrical stimulation of greater occipital nerve (NITESGON) improves memory in healthy young (18–25 years) [15] and older (>65 years) [16] participants up to 28 days after stimulation. In the latter study, NITESGON was utilized in an older population to determine if stimulation during an associative memory task can optimize associative memory performance up to 28 days later. Thirty subjects between the ages of 55 and 70 years were enrolled and randomly assigned to active or sham NITESGON group. Active or sham NITESGON was delivered during the study phase at visit 1 of the associative memory task, and participants were asked to return 7-and 28-days later to measure memory recall. During visit 1, participants learned a list of 50 Swahili-English word pairs (e.g., mashua-boat) across a total of 3 blocks for each study (S) and test (T) phase. The study phase of each block consisted of 50-word pairs followed by a test phase of the 50 words, in which participants were asked to type the correct English translation for each Swahili word. Participants were then dismissed and returned for the test 7-days and 28-days later (recall phase). During this test, subjects were shown each Swahili word and were asked to type the correct English translation. This was identical to the test phase from the first visit. Participants that received active stimulation exhibited increased words recalled on days 7 and 28 compared to participants that received sham stimulation (Day 7: η^**2**^ = .21; Day28: η^**2**^ = .14). These findings suggest that NITESGON enhances memory performance up to 28-days after a single session. With these results, we propose that NITESGON could mitigate memory loss and rate of decline in the earliest stages of Alzheimer's disease.

Results also demonstrated that NITESGON promotes noradrenaline (NA) release though LC activation, followed by enhanced communication between the LC and hippocampus. NITESGON induced synaptic plasticity then modulates memory with lasting effects by strengthening memory consolidation after encoding, resulting in upregulated memory performance [15]. Furthermore, we were able to show that NITESGON induces gamma changes in the medial temporal lobe immediately after NITESGON, which was correlated with successful recall several days after stimulation. This latter finding suggest that gamma oscillations can potential be use as a biomarker for successful recall.

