### Study design

2.3

This study is designed as a prospective, double-blind, placebo-controlled, randomized parallel-group study that will be completed at Trinity College Dublin, Ireland. A total of 100 individuals with amnestic mild cognitive impairment (aMCI) based on diagnostic criteria described by the National Institute on Aging and Alzheimer's Association [17] will be recruited from Alzheimer's Ireland. Subject will receive a (real or control) non-invasive transcutaneous electrical stimulation of the greater occipital nerve (NITESGON) procedure. After providing written informed consent, subjects will be assigned to one of four groups. One group will receive active NITESGON, while the three groups will be control groups. One group will receive sham NITESGON (inactive control), while a second group will receive active NITESGON with local anesthesia (active control; local nerve anesthesia group) and a third group will stimulate the C5/C6 nerve (active control; same sensation different nerve). We will include three control groups so that we are able to verify that the effect is real, location specific and cannot be associated to a sensation effect.

We have opted to use a parallel-group design as it is unclear what the carry-over effect and/or wash-out period will be for NITESGON. Subjects will be randomized after screening evaluation and will be assigned to receive one of the four possible types of NITESGON. To eliminate subjective bias, all subjects and the investigator testing the endpoint measures will be blinded to the type of intervention. The researcher who will control the NITESGON device will not be involved in instructing the participant; this will be performed by a second researcher who will be blind to the stimulation protocol. The primary outcome will be change in memory performance as measured by a word association task, measured at baseline (T0), 7 days after NITESGON (T1) and after 28 (T2) days after NITESGON. Secondary outcomes include changes in resting EEG, which will be assessed immediately before and after NITESGON (see Fig. 1 and Table 1).

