### Statistical analysis

2.10

For our calculations, we will use the normal distribution assumption, which we will test using a normal plot and goodness of fit test. If violations are found, non-parametric tests or transformations will be utilized. Variance equivalence will be tested using the F-test. Our protocol is designed to assure sample independence, and adherence will be closely monitored. Before beginning the main statistical analyses, screening variable levels (e.g., age, sex, education, disease onset, mood) across groups will first be considered to assess group equivalence. If the groups are not balanced on any baseline characteristics, these factors will be considered as co-variate in later multivariate regressions.

The efficacy of NITESGON will be assessed on word recall by testing its effect on the mean change over time relative to the control groups. Memory task performance will be analyzed over time at baseline, and 7 and 28 days after NITESGON, and across groups. Statistically, these tests will be single degree-of-freedom interaction contrasts from a general mixed linear model containing both within- and between-subject variance components. All tests will be based on directional hypotheses in favor of improvements due to NITESGON on the behavioral assessment. We expect large behavioral effects based on our previous studies in control and patient populations.

*EEG.* sLORETA statistical contrast maps between pre and post NITESGON will be calculated for the sham and active groups through multiple voxel-by-voxel comparisons in a logarithm of F-ratio [27]. Statistical analysis is based on estimating, via randomization, the empirical probability distribution for the max-statistic under the null hypothesis comparisons [28]. This methodology corrects for multiple testing (i.e., for the collection of tests performed for all voxels and for all frequency bands). Due to the non-parametric nature of the method, its validity does not rely on any assumption of Gaussianity [28]. A comparison will be made between the contrast map for the active and sham group. The significance threshold is based on a permutation test with 5000 permutations. In addition, the statistical contrast map (pre-post) will be correlated with the difference on in memory improvement.

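### The EEG–memory correlation uses raw recall in one section and an improvement with no stated reference point in another, and neither version accounts for pre-stimulation memory ability

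*Protocol article*

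**What the plan says.** The protocol article describes the EEG–memory association in two places.

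- **Secondary outcome measures (2.7.2, item 1):** resting EEG taken before and after stimulation "will be correlated with the recall of the word-association task 7 (T1) and 28 (T2) days after NITESGON". The memory variable is the recall score at follow-up.
- **Statistical analysis (2.10, EEG paragraph):** "In addition, the statistical contrast map (pre-post) will be correlated with the difference on in memory improvement". The memory variable is now a difference or improvement. The EEG variable is the pre-to-post contrast: "sLORETA statistical contrast maps between pre and post NITESGON will be calculated for the sham and active groups".

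Two other statements bear on what improvement means. Study design (2.3) says "The primary outcome will be change in memory performance as measured by a word association task". Outcome assessment (2.7) says "Recall will be assessed using the word-association task during the learning phase at visit one (T0"), followed by the day-7 and day-28 tests. By Intervention (2.6), current is applied during each of the three study phases, and by Study procedure (2.5) recall is tested after each of those blocks.

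Baseline variables have two stated uses. The covariate rule in 2.10 reads "If the groups are not balanced on any baseline characteristics, these factors will be considered as co-variate in later multivariate regressions". The control tests in 2.7.2 (item 4), CVLT-II among them, are collected before stimulation and serve to check that groups do not differ.

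**The concern.** The correlation compares individuals, and EEG response is not randomised within an arm. Randomisation therefore does not protect it from a shared cause such as disease severity. Entry allows MoCA scores from 18 to 25 and a CDR global score of 0.5 or greater, so memory ability will vary. A milder participant could show both a larger gamma response and better recall without the one explaining the other.

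Both stated uses of baseline variables concern differences between groups. An imbalance rule does nothing about confounding between individuals inside a correlation, and the issue arises within a single arm as well as across arms.

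The two descriptions also differ in their exposure to this problem. Raw recall carries the participant's general memory level in full, whereas a change score removes the stable part of it. The reader cannot tell which will be analysed, or from what reference point. The natural reference, T0 word recall, is obtained after stimulated study, so in the stimulated arms it may already carry part of the effect under study.

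What is at stake is the interpretation of the mechanistic result. The Background says of earlier work that "gamma oscillations can potential be use as a biomarker for successful recall", and the second hypothesis in Aims (2.1) links gamma increase to recall at 7 and 28 days.

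**Working it through.** **The plan's own figure.** There is none for this analysis. The 76 and 100 in Sample size (2.9) refer to the comparison between groups.

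**Number of participants.** Section 2.10 states contrast maps for the active and sham groups only: 25 + 25 = 50. With the 20% dropout allowed in 2.9, 50 × 0.8 = 40.

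**1. Raw-recall form (2.7.2).** Assumptions, not in the documents: memory ability correlates a = 0.5–0.7 with later recall and g = 0.2–0.4 with gamma change, and there is no direct link between gamma and recall. The expected correlation is then r = a × g. For one two-sided 5% test, the rejection rate is approximately Φ(z − 1.96) + Φ(−z − 1.96), with z = atanh(r) × √(n − 3). Simulation with 40,000 replicates per cell gave:

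| a, g | r = a × g | n = 40 | n = 50 |
|---|---|---|---|
| 0.5, 0.2 | 0.10 | 9% | 11% |
| 0.6, 0.3 | 0.18 | 20% | 24% |
| 0.7, 0.4 | 0.28 | 43% | 51% |

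Check by formula for the middle row at n = 50: atanh(0.18) = 0.182; 0.182 × √47 = 1.25; Φ(−0.71) + Φ(−3.21) ≈ 0.24.

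**2. Change form (2.10).** What matters here is whether severity relates to the change in recall.

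- If it does not, the expected correlation is 0 and rejection is about 5%, even when severity drives the EEG response.
- If change in recall and gamma change each correlate 0.3 with memory ability, r = 0.3 × 0.3 = 0.09; 0.0902 × √47 = 0.62; Φ(−1.34) + Φ(−2.58) ≈ 0.095. The simulated rate was 9.6%, so about 9–10% at n = 50.

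**3. Both forms in one model.** A separate simulation (2,000 replicates, n = 50, assumed severity effects, no direct link) modelled EEG before and after stimulation and recall at T0 and day 7:

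| Severity affects | EEG change vs raw recall | EEG change vs recall change |
|---|---|---|
| EEG level only | 5% | 4% |
| EEG response too | 37% | 4% |
| EEG response and forgetting | 49% | 10% |

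The last cell can be checked by hand. EEG change had severity effect 0.3 and noise variance 0.5, so its correlation with severity is 0.3/√0.59 = 0.39. Recall change had severity effect 0.3 and total variance 0.09 + 0.84 + 0.51 = 1.44, giving 0.3/1.2 = 0.25. The product is about 0.10.

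**4. What adjustment achieves.** If the baseline score correlates q with true memory ability, the remaining partial correlation is a·g·(1 − q²)/√[(1 − a²q²)(1 − g²q²)]. For the top case (0.7, 0.4):

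- q = 1: residual 0; rejection 5%.
- q² = 0.8: 0.28 × 0.2/√(0.608 × 0.872) = 0.077; rejection about 8% at n = 50.
- q = 0.7: 0.28 × 0.51/√(0.760 × 0.922) = 0.17; rejection about 21% at n = 50, against 51% unadjusted.

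Adjustment reduces the inflation, and removes it only if the score measures memory ability without error.

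**The case against.** The strongest case on the other side starts from section 2.10, which is where the method is stated. It already uses change on both sides, and section 2.3 defines the outcome as change. A reader might infer from 2.7.2 that the plan ignores each participant's own starting level, so that severity alone would produce a gamma–recall result. The documents do not support that. On the natural reading of 2.10 a stable severity level is differenced out, and false rejection stays near 5% unless severity drives both the EEG response and the rate of forgetting. Nothing in the documents shows that severity relates to gamma change at all. Larger inflation figures for 100 participants (up to 81% under the same assumptions) do not fit a section whose maps are stated only for the active and sham groups.

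It is also fair to say that covariates for a secondary analysis are commonly left to the SAP, that the biomarker remark concerns earlier work and is tentative, and that no section claims gamma predicts recall beyond baseline memory.

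These arguments limit the point without removing it. The article itself gives two different memory variables, and the improvement in 2.10 has no stated reference point, so 2.10 cannot simply be taken to override 2.7.2. If T0 word recall is the reference, it is measured after stimulated study. Accelerated forgetting is the premise of the trial, so forgetting that varies with severity within aMCI is plausible, though not shown; in that case the change score is confounded too. And the uses of baseline data that are stated address only group differences.

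**Conclusion.** The point holds as a minor one about a secondary mechanistic analysis. Sections 2.7.2 and 2.10 give different memory variables and must be reconciled, and neither version accounts for pre-stimulation memory ability.

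Under the assumed correlations, the raw-recall form falsely rejects about 9–43% of the time at n = 40 and 11–51% at n = 50. The change form is about 5%, rising to about 9–10% at n = 50 if forgetting also varies with severity. These figures are for one nominal two-sided 5% test of a participant-level correlation; the article does not say how a contrast map is to be correlated with a score. They show a possible bias, not a demonstrated one, because the link from severity to EEG response is an assumption throughout. The primary comparison of recall between randomised groups is unaffected.

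**What to change.** In 2.7.2 (item 1) and in the EEG paragraph of 2.10:

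1. Name one memory variable, used in both places. If it is a change, state its reference point and acknowledge that T0 word recall follows stimulated study.
2. Estimate its association with participant-level medial temporal gamma change by regression or partial correlation, adjusted for the pre-stimulation (T0) CVLT-II score and age.
3. Report the unadjusted correlation as descriptive.

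The cost is a sentence or two of wording and one or two degrees of freedom. CVLT-II is already collected before stimulation and age is already a screening variable, so no new data are needed. The report should say that adjustment lessens confounding by severity without eliminating it, because CVLT-II measures memory with error.

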**Fig. 1 fig1:**
[figure not shown]
Participant flow through study.

**Table 1 tbl1:** Data collection timepoints.

	T0	T1	T2
	Baseline	7 days after NITESGON	28 days after NITESGON
Word association task	x	x	x
Neurophysiology	x		
Adverse events	x		
Blinding			x
Control assessments	x		

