### Intervention

2.6

NITESGON will be delivered by a specially developed, battery-driven, constant current stimulator with a maximum output of 10 mA (http://www.neuroconn.de) via a pair of saline-soaked surface sponges (35 cm^2^) on the scalp. One electrode will be placed over the left and right C2 dermatomes each. A constant current of 1.5 mA intensity will be applied during each of the 3-study phases (i.e., 250 s x 3 blocks). For sham NITESGON, placement of the electrodes will be identical to active NITESGON. A third group (local nerve anesthesia group) will receive NITESGON, but we will use a topical skin anesthetic (lidocaine/prilocaine cream) to reduce any potential contribution from transcutaneous stimulation of peripheral nerves. This lidocaine/prilocaine preparation blocks sodium channels in peripheral nerves in the skin and thereby stabilizes the membrane potential and increases the threshold for firing an action potential [15,19]. For the fourth control group (different nerve group), the electrodes will be placed over cervical nerves five and six, to mimic the sensation, but change the location. For both the third and fourth control group, we will apply the same current as active NITESGON. NITESGON will first be switched on in a ramp-up fashion over 30 s. For sham, the current intensity (ramp down) will gradually be reduced (over 5 s) as soon as NITESGON reaches a current flow of 1.5 mA. The rationale behind this sham procedure is to mimic the transient skin sensation at the beginning of active NITESGON without producing any conditioning effects on the brain.

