*TES Adverse events.* A comparison will be conducted between the active and sham group using a one-way ANOVA with stimulation (active NITESGON vs sham NITESGON) as independent variable and adverse events as dependent variable.

*Blinding.* A Chi-square test will be conducted comparing actual stimulation (active NITESGON vs sham NITESGON) versus participants' expected stimulation (active NITESGON vs sham NITESGON).

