## Discussion

3

ALF is an early pre-symptomatic feature of autosomal dominant Alzheimer's disease, which appear to pre-date other amnestic deficits and underpin subjective memory complaints in AD [29]. Walsh and colleagues found that aMCI subjects showed greater loss of information over 1 week than controls and that delayed memory recall deficits in aMCI subjects appeared to be related to impaired consolidation when controlling for the initial learning [30]. Similarly, we predict that individuals with aMCI will perform significantly worse 7 days after initial learning of the word association task. The objective of the current project is to determine if NITESGON is an effective intervention to improve memory recall and therefore mitigate ALF in individuals with aMCI.

To the best of our knowledge, there have been no trials evaluating the effect of electrical stimulation of the greater occipital nerve on episodic memory in aMCI populations. LC degeneration has been associated with aMCI [7,[10], [11], [12], [13], [14]], with LC neuropathology detectable as early as 10 years before neurocognitive signs [[31], [32], [33]]. Furthermore, NITESGON can upregulate NA through the LC-NA pathway. Therefore, this approach could potentially benefit individuals with aMCI. The secondary outcome measures will examine mechanisms that may underlie the memory effect these populations.

Early identification of disease combined with effective intervention is the optimal strategy to alleviate memory impairments in aMCI subjects and ultimately maintain quality of life. NITESGON has the potential to improve memory recall by mitigating the disruption of memory consolidation in individuals with aMCI. This new memory management system is non-invasive, non-pharmacological, safe, with few adverse side effects, portable and can be readily applied at a reasonable cost. In addition, NITESGON can be implemented in individuals on a variety of different medications that have not been responsive to other treatments.

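### Side effects are solicited only at the end of the stimulation visit, and only active and sham are formally compared; asking again at days 7 and 28 and tabulating all four arms would be a minor, cheap improvement.

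*Protocol article*

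**What the plan says.** Adverse events are listed as a secondary outcome in section 2.7.2 of the protocol article. An exit questionnaire covers ten symptoms, from headache and neck pain to "skin redness, sleepiness, trouble concentrating, mood changes) at the end of T0". Table 1 agrees: the row "Adverse events x" has its single mark under T0, and the T1 and T2 cells are blank.

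Participants come back twice. Section 2.7.1 states: "Subjects will then be dismissed and asked to return for a follow-up test 7 days and 28 days later (recall phase"). Section 2.7.2 also puts the blinding question at T2. Its text places the control assessments, including the Beck depression and anxiety inventories, at T0 and T2, although Table 1 marks them at T0 only.

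For the analysis, section 2.10 says: "A comparison will be conducted between the active and sham group using a one-way ANOVA". It mentions neither the other two arms nor any later time point. Section 2.6 gives both of those arms the same current as the active arm. Section 2.11 promises summary statistics on all variables. The Discussion describes the method as "non-invasive, non-pharmacological, safe, with few adverse side effects".

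**The concern.** Several symptoms on the trial's own list (headache, neck pain, skin redness, sleepiness, mood change) could start after the participant goes home, or start during the visit and last longer than it. The schedule has no planned point at which to ask about either, although two later visits already exist. Section 3 says the authors know of no earlier trial of greater occipital nerve stimulation on episodic memory in aMCI, so the trial's own tolerability data will be the direct evidence in this population.

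The second part is coverage of the arms. Three arms receive the full current, but only one of them enters the stated comparison. The other two add exposures of their own: a topical anaesthetic cream in one and a different electrode site in the other. Section 2.6 says the cream raises the firing threshold of nerves in the skin. It is a reasonable inference, though not something the article states, that skin symptoms in that arm may be muted when asked about on the day.

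What is at stake is the completeness of the safety description. No efficacy result, error rate or sample size depends on it.

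**Working it through.** No design figure rests on this schedule, so there is no power or sample-size figure to reproduce. The check compares the schedule statements and then does timing and count arithmetic from the article's own inputs.

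**1. Is any other collection described?** Section 2.7.2 and Table 1 agree on T0 only. Section 2.8 (Safety) reviews earlier literature and sets out no collection in this trial. Section 2.4 allows withdrawal for urgent medical reasons without describing event recording. Section 2.10 adds no time point. The only later measures that overlap the list are control assessments at T2: the two Beck inventories bear on mood, and the attention and executive tests bear loosely on concentration. None is collected as an adverse event.

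**2. How long is the window on the day?** Inputs: 50 pairs shown for 5 s each, a 30 s rest after each study period, and at most 50 test items at 16 s each (section 2.7.1); stimulation time "i.e., 250 s x 3 blocks" (section 2.6).

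- Study phase: 50 × 5 s = 250 s, which reproduces the section 2.6 figure. Total stimulation: 3 × 250 = 750 s.
- Rest plus test after the last stimulation phase: at most 30 + 50 × 16 = 830 s = 13.8 min. This is an upper bound, because block 3 tests only items not yet recalled. The post-stimulation EEG adds a length that is not stated.
- Whole three-block task: at most 3 × (250 + 30 + 800) = 3,240 s = 54 min.
- Follow-up: 28 × 24 × 60 = 40,320 min. The whole task is 54 / 40,320 = 0.13% of this, and the part after stimulation is 13.8 / 40,320 = 0.03%, EEG time excluded.

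**3. Who is in the stated comparison?** Inputs: 25 per group (section 2.5), with the same current in the active, anaesthesia and C5/C6 arms (section 2.6).

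- Full-current participants: 3 × 25 = 75.
- Outside the active-sham comparison: 2 × 25 = 50, or 50 / 75 = 67%.

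**4. Could later questioning find anything at this sample size?** The documents give no rate of delayed symptoms, so the rates here are assumptions. The probability of at least one case among 25 active participants is 1 − (1 − p)^25:

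| Assumed rate p | Probability of at least one case in 25 |
|---|---|
| 2% | 40% |
| 5% | 72% |
| 10% | 93% |

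These are chances that a case occurs. Whether it is reported depends on recall.

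**The case against.** The strongest defence is that the schedule is a deliberate choice with a stated rationale. There is one session of 750 s at 1.5 mA, or 1.5 mA × 750 s = 1.125 C before ramps. That is well inside the range reviewed in section 2.8 (up to 40 min, 4 mA and 7.2 C). The same section reports that most effects are mild and short-lived, and that no active-sham difference in side effects has been seen so far. Safety is not among the aims in section 2.1. The remedy is also imperfect: these participants are enrolled for a disorder of rapid forgetting, and they would be asked to recall mild symptoms over gaps of 7 and then 21 days. All of this stands, and it keeps the point minor. It does not remove it: most effects being short-lived is not all of them, and the literature in section 2.8 mainly concerns electrical stimulation in general.

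Four stronger readings are tempting and are not supported.

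- **A reader might infer that later symptoms are never recorded.** The article schedules one solicited questionnaire and does not say that other events go unlogged. Spontaneous reporting may be in the full protocol, which is not shown. A symptom that starts during T0 is caught there; what is missed is how long it lasts. Mood may be picked up indirectly at T2.
- **A reader might infer that the other two full-current arms yield no safety data.** Section 2.7.2 does not restrict the questionnaire to any arm, and section 2.11 promises summaries of all variables. What is absent is a stated comparison and any commitment to tables by arm.
- **A reader might infer that ANOVA is the wrong method.** The article does not say how the questionnaire is scored. For graded ratings or a sum score, comparing two means is defensible.
- **A reader might measure the gap by the upper confidence limit when no events are seen.** That limit depends on the number of participants, not on when they are asked, and would be the same after the change.

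**Conclusion.** The point holds in a limited form. The text and Table 1 agree that side effects are solicited once, on the stimulation day. No scheduled recording is described for the following 28 days, although two visits fall within them. The formal comparison covers one of the three full-current arms, which leaves 50 of 75 planned participants with at most general summary statistics. Both are stated choices, not detail left to a fuller document.

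The size is small. It is a gap in safety ascertainment with a modest expected yield and no bearing on the primary analysis. The conclusion assumes that no later solicited questionnaire exists outside the article, and that at least some listed symptoms can begin or persist after the visit. The documents do not quantify the latter.

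**What to change.** 1. Give the same questionnaire at T1 and T2, asking about symptoms since the last visit. Place it after the recall test so that the primary outcome is not disturbed.
2. Mark adverse events under T1 and T2 in Table 1, and amend section 2.7.2 to match.
3. In section 2.10, keep the active-sham comparison and add a table of each symptom by arm for all four arms, as counts with exact 95% confidence intervals, shown separately for T0, T1 and T2.

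The cost is a few minutes at two visits that already take place, plus one table; there is no extra visit and no change in sample size. The drawback is incomplete recall of mild symptoms in this population, so the T1 and T2 counts should be read as likely under-reports and kept apart from the T0 data.
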